#### **8.5.4. Regulatory Reporting Requirements for SAEs**

- Prompt notification by the investigator to the sponsor of an SAE is essential so that legal obligations and ethical responsibilities towards the safety of participants and the safety of a study intervention under clinical investigation are met.
- The sponsor has a legal responsibility to notify both the local regulatory authority and other regulatory agencies about the safety of a study intervention under clinical investigation. The sponsor will comply with country-specific regulatory requirements relating to safety reporting to the regulatory authority, Institutional Review Boards (IRB)/Independent Ethics Committees (IEC), and investigators.
- An investigator who receives an investigator safety report describing an SUSAR or other specific safety information (e.g., summary or listing of SAEs) from the sponsor will review and then file it along with the summary of product characteristics and will notify the IRB/IEC, if appropriate according to local requirements.

## 9. Statistical Considerations

### 9.1. Statistical Hypotheses

This study is designed to show that the antiaging effect of starting metformin superior to placebo at week 96 in HIV-1 infected ART-experienced subjects.

### 9.2. Sample Size Determination

Approximately 80 participants will be screened to achieve 30 randomly assigned to study intervention for an estimated total of 30 evaluable participants per intervention group.

A maximum of 40 participants will be randomly assigned to study intervention such that approximately 30 evaluable participants complete the study.

**Note:** “Enrolled” means a participant’s, or their legally acceptable representative’s, agreement to participate in a clinical study following completion of the informed consent process. Potential participants who are screened for the purpose of determining eligibility for the study, but do not participate in the study, are not considered enrolled, unless otherwise specified by the protocol.

We do not have prior information to estimate the sample size accurately. With 30 subjects per group, a confidence level of 95% we would be able to detect with a power of 80% an effect size greater than 0.8.

**Note:** “Enrolled” means a participant’s, or their legally acceptable representative’s, agreement to participate in a clinical study following completion of the informed consent process and screening. Potential participants who are screened for the purpose of determining eligibility for the study, but do not participate in the study, are not considered enrolled, unless otherwise specified by the protocol.

### 9.3. Analysis Sets

For the purposes of analysis, the following analysis sets are defined:

| Participant Analysis Set | Description                                                                                                                                            |
|--------------------------|--------------------------------------------------------------------------------------------------------------------------------------------------------|
| Randomized               | Participants who were assigned to one group of study intervention                                                                                      |
| Evaluable                | Participants who received at least 1 dose of study intervention                                                                                        |
| Safety                   | All randomized participants who are exposed to study intervention. Participants will be analyzed according to the intervention they actually received. |

| Defined Analysis Data Sets                                    | Description                                                                                                                                  |
|---------------------------------------------------------------|----------------------------------------------------------------------------------------------------------------------------------------------|
| Analysis set for primary estimand: Intention-to-treat-exposed | All randomized participants who are exposed to study intervention. For participants who discontinue study intervention and/or receive rescue |

|              |                                                                                                                                                                                       |
|--------------|---------------------------------------------------------------------------------------------------------------------------------------------------------------------------------------|
|              | therapy, all post discontinuation or post rescue observations will be included in the analysis set.                                                                                   |
| Per protocol | All randomized participants. For participants who discontinue study intervention and/or receive rescue therapy, post discontinuation or post rescue observations will not be included |

#### 9.4. Statistical Analyses

The statistical analysis plan will be finalized prior to database lock and it will include a more technical and detailed description of the statistical analyses described in this section. This section is a summary of the planned statistical analyses of the most important endpoints including primary and key secondary endpoints.

##### 9.4.1. General Considerations

Efficacy results that will be deemed to be statistically significant after consideration of the type I error control. To determine the treatment effect between study intervention groups, the estimate of the between-group treatment effect (with a nominal 95% CI) for the primary endpoint will be estimated and plotted within each group.

At least one laboratory value or vital sign obtained subsequent to at least one dose of study treatment is required for inclusion in the analysis of the respective safety parameter. To assess change from baseline, a baseline measurement is also required.

Two study periods are defined: intervention period (96 weeks since randomization) and follow-up phase (from week 96 to week 144)

##### 9.4.2. Primary Endpoint(s)

Mixed models for repeated measures will be used to assess treatment differences of the change EAA measured by Phenoage at every visit. The repeated measures analysis will assume that the treatment difference can vary between visits (ie. treatment\*visit interaction will be included in the model) and separates estimates and 95% confidence intervals will be produced at each visit. The model will also assume that the effect of baseline value for the endpoint can vary between visits (ie. baseline value\*visit interaction will be included in the model) and will adjust for other potential confounders.

##### 9.4.3. Secondary Endpoint(s)

Mixed models for repeated measures will be used to assess treatment differences of the secondary endpoint previously described.

##### 9.4.4. Analysis

Safety and tolerability will be assessed by clinical review of all relevant parameters including AEs, events of clinical interest, laboratory values and vital signs.

For continuous measures such as changes from baseline in laboratory and vital signs parameters, summary statistics for baseline, on-treatment, and change from baseline values will be provided

by treatment group in table format. In addition, summary statistics for the difference between treatment groups will also be provided. Incidence and severity of adverse events and laboratory abnormalities will be compared by treatment group using  $\chi$ -squared test.

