|-----------------------------------------------------------------------------------------------------------------------------------------------------------------------------------|-------------------------------------------------------------------------------------------------------------------------------------------------------------------------------------------------------------------------------|
|                                                                                                                                                                                   | 
expression, superoxide dismutase 1 - 2 levels, <math>\gamma</math>H2AX histone levels.
 
 
Other inflammatory and pro-coagulant biomarkers: IL-1 beta, TNF-alfa, D-dimer
 
 |
| 
 
To evaluate the effect of metformin compared to placebo as assessed by the frailty phenotype improvement at week 48, 96 and 144
 
 | 
 
Changes in the following frailty battery: Fried frailty index, grip strength, walking speed and short physical performance battery
 
                                          |
| 
 
To evaluate the security of metformin compared to placebo as assessed by lab parameters at week 24, 48, 72, 96, 120 and 144
 
     | 
 
Changes in creatinine
 
                                                                                                                                                       |
| 
 
To evaluate the effect of metformin compared to placebo as assessed by the viral reservoir parameters' changes at week 48
 
       | 
 
Changes in integrated and total (Gag) HIV-DNA
 
Changes in CA US HIV-RNA
 
Changes in intact proviral DNA
 
                                                     |

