#### **4.2.2. Rationale for endpoints**

The primary endpoint selected in this study, differences in epigenetic age acceleration, is intended to demonstrate the efficacy of metformin relative to placebo.

This is a phase II, double blinded, placebo controlled, single centre randomized clinical trial to gain preliminary evidence about the efficacy and safety of metformin for reversal of accelerated epigenetic aging in persons  $\geq 50$  years living with HIV and with suppressed virological replication. We have chosen  $\geq 50$  years because this is the consensus cut-off that defines to define medically advanced age in HIV-infected people (AIDS Research and Human Retroviruses 2012; 28:1000–1006). This is the first time that the efficacy of an intervention against accelerated/acceluated aging is going to be measured by epigenetic clocks in people living with HIV

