### **Assessment of Intensity**

The investigator will make an assessment of intensity for each AE and SAE reported during the study

- The intensity of the AE will be graded following the DAIDS grading table for Severity of AEs.(43)
- AE severity grading scale ranging from grades 1 to 5 with descriptions for each AE based on the following general guidelines:
  - Grade 1 indicates a mild event (An event that is easily tolerated by the participant, causing minimal discomfort and not interfering with everyday activities)
  - Grade 2 indicates a moderate event (An event that causes sufficient discomfort to interfere with normal everyday activities.)
  - Grade 3 indicates a severe event (An event that prevents normal everyday activities. An AE that is assessed as severe should not be confused with an SAE. Severe is a category utilized for rating the intensity of an event; and both AEs and SAEs can be assessed as severe.

An event is defined as ‘serious’ when it meets at least 1 of the predefined outcomes as described in the definition of an SAE, NOT when it is rated as severe.

  - Grade 4 indicates a potentially life-threatening event
  - Grade 5 indicates death
- If the severity of an AE could fall in either one of two grades (i.e., the severity of an AE could be either grade 2 or grade 3), sites should select the higher of the two grades.

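### Section 9.4.4 compares ordered adverse-event grades with a chi-squared test that ignores their order, and names no risk difference or interval for event counts at about 30 per arm

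*Protocol*

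**What the plan says.** Section 4.2.2 describes the trial as one "to gain preliminary evidence about the efficacy and safety of metformin", so safety is part of its stated purpose.

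Section 9.4.4 then sets out the safety analysis in three parts:

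- An overall approach: "Safety and tolerability will be assessed by clinical review of all relevant parameters including AEs, events of clinical interest, laboratory values and vital signs".
- Tables by group for laboratory and vital-sign measures on a continuous scale, where "summary statistics for the difference between treatment groups will also be provided".
- For event counts and grades: "Incidence and severity of adverse events and laboratory abnormalities will be compared by treatment group using" a chi-squared test.

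The severity scale is in Appendix 4 (10.4.3, Assessment of Intensity): "AE severity grading scale ranging from grades 1 to 5", running from mild to death. Laboratory safety also appears as a secondary objective in section 3, "To evaluate the security of metformin compared to placebo as assessed by lab parameters". Its endpoint is change in creatinine, so it falls under the mixed model that section 9.4.3 gives for secondary endpoints.

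For the number of participants, section 9.2 takes 30 per arm, 95% confidence and 80% power, and gives as detectable "an effect size greater than 0.8". No power is given for any safety comparison.

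**The concern.** The chi-squared sentence covers two different questions.

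**Severity.** The question is whether metformin moves participants towards worse grades. Pearson's chi-squared asks only whether the two arms have different distributions over unlabelled categories. With five levels (none, grades 1 to 4) it spreads its sensitivity over 4 degrees of freedom, and with four levels over 3. A test that uses the order puts it into the one direction of interest.

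**Incidence.** A chi-squared test on a 2×2 table is a valid test, but its p-value does not say how large an excess risk remains compatible with the data. At about 30 per arm that range is wide, and section 9.4.4 names no estimate or interval for these counts. By contrast, sections 9.4.1 and 9.4.2 specify 95% intervals for the primary efficacy endpoint.

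At stake is how informative the comparison of adverse events and laboratory abnormalities will be in a trial that offers preliminary safety evidence over 96 weeks of treatment.

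**Working it through.** **Inputs from the protocol.** 30 per arm (9.2); 1:1 allocation (6.3); ordered grades 1 to 5 (10.4.3); chi-squared test (9.4.4). Section 9.2 gives only a 95% confidence level, so a two-sided 5% test is assumed. The protocol gives no event rates and no grade distribution; those below are assumptions.

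**The plan's own figure.** The only power figure in the protocol concerns a standardised effect on a continuous endpoint. With 30 per arm, two-sided 5% and 80% power, the detectable effect by the two-sample t-test is 0.74, and power at 0.8 is 86%. The stated 0.8 is therefore conservative. It concerns efficacy and has no bearing on this point. There is no safety figure to reproduce.

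**Severity: one worked case.** Assume placebo worst-grade shares of 40, 30, 20, 8 and 2% for none and grades 1 to 4. Under proportional odds, each cumulative odds is divided by the odds ratio. For none, with odds ratio 3: odds = 0.40/0.60 = 0.667; 0.667/3 = 0.222; share = 0.222/1.222 = 18.2%. The metformin shares become 18.2, 25.6, 31.2, 19.2 and 5.8%. Simulated power at 30 per arm, Pearson 2×5 against a linear-trend test on the grades:

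| Odds ratio | Pearson | Trend |
|---|---|---|
| 1 | 4% | 5% |
| 2 | 17% | 31% |
| 3 | 39% | 62% |
| 4 | 61% | 83% |

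A repeat simulation of the odds-ratio-3 case with the Wilcoxon rank-sum test gave 41% for Pearson and 64% for Wilcoxon.

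**Severity: across assumptions.** Four assumed placebo distributions (three with five levels, one with four), 8,000 simulated trials per scenario, odds ratio 3:

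- Five levels: Pearson 39.2, 37.9 and 38.2%; Wilcoxon 63.3, 63.0 and 63.1%.
- Four levels: Pearson 46.2%; Wilcoxon 63.2%.

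The loss is 17 points (63.2 − 46.2) to 25 points (63.0 − 37.9). At odds ratio 2.5 the ranges are 26–33% against 47–49%; at 4, 60–68% against 82–83%. With no effect, rejection rates are 3.2–5.2% for Pearson and 4.3–4.9% for Wilcoxon, so the gain is not bought with a higher false-positive rate.

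**Incidence: chance of a non-significant result.** Power = Σ Bin(x; 30, p1) × Bin(y; 30, p2) over all 2×2 tables with Pearson p ≤ 0.05, without continuity correction. The miss rate is 1 − power:

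| Assumed rates | Missed |
|---|---|
| 10% v 20% | 81% |
| 5% v 15% | 74% |
| 20% v 40% | 61% |
| 10% v 30% | 50% |
| 30% v 60% | 34% |

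Section 9.2 also gives a maximum of 40 randomised. If that is a total, 20 per arm gives 86% for 10% v 20% and 71% for 20% v 40%. The early safety review in 10.1.5 equates 30 participants with half the trial, which supports 30 per arm.

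**Incidence: what an interval adds.** Take 6/30 on metformin and 3/30 on placebo.

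- Chi-squared = 60 × (6×27 − 24×3)² / (30 × 30 × 9 × 51) = 60 × 8,100 / 413,100 = 1.18, p = 0.28.
- Wilson 95% limits: 6/30 gives 0.095 to 0.373; 3/30 gives 0.035 to 0.256.
- Newcombe lower limit: 0.10 − √[(0.200 − 0.095)² + (0.256 − 0.100)²] = 0.10 − 0.188 = −0.088.
- Newcombe upper limit: 0.10 + √[(0.373 − 0.200)² + (0.100 − 0.035)²] = 0.10 + 0.185 = 0.285.

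The non-significant result is compatible with anything from 9 points fewer to 29 points more events on metformin.

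**The case against.** **Safety is not left to this test.** A reader might infer that the protocol would take a non-significant chi-squared result as evidence of safety, or that its safety conclusion rests on this test. The documents support neither. No decision rule is tied to the p-value. Section 9.4.4 starts from clinical review and adds between-group differences for continuous measures. Creatinine is analysed by the mixed model of 9.4.3. Section 10.1.5 adds continuous review by a sponsor committee, plus an early aggregate review that looks for deaths and for grade 3 events in more than two participants. This stands, and it confines the point to adverse-event and laboratory-abnormality counts and grades.

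**Low power for incidence is a sample-size matter.** This also stands. A risk-difference interval at 30 per arm detects no more harm than the test does. Nor can one say that most relevant harms are missed: relevance is undefined, the rates are assumed, and large differences would often be found. The incidence part is a reporting gain only.

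**Intervals may be in the SAP.** Section 9.4 calls itself a summary and refers to a more detailed plan, which is not available here. The absence of an interval is therefore not in itself an error. The choice of a chi-squared test for severity is different: the protocol states it, and a plan that elaborates section 9.4 would carry it forward.

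**The severity loss depends on the table.** Section 9.4.4 does not say how grades will be tabulated. If they were cut into two classes, the test would have 1 degree of freedom and the loss would not arise as calculated. Proportional odds is also an alternative that suits rank tests. Both qualifications stand. Dichotomising would discard the grade order by another route.

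**Conclusion.** The point holds for adverse-event and laboratory-abnormality counts and grades, and not for safety assessment as a whole.

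Severity is the stronger part. When grades are analysed on their multi-level scale, the stated test ignores their order. At 30 per arm it loses about 17 to 25 points of power at an odds ratio of 3 (about 38–46% against about 63%), with both tests at about 5% or less under no effect. The size of the loss rests on assumed placebo distributions and a proportional-odds shift; that Pearson's test ignores order does not depend on either.

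For incidence, the chi-squared test is valid but uninformative alone. A true 10% versus 20% is missed 81% of the time, and a non-significant 6/30 versus 3/30 leaves an interval of −9 to +29 points. This follows from the sample size and assumed event rates. The gain from an interval is that the remaining uncertainty is shown.

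**What to change.** Amend the chi-squared sentence in 9.4.4 in two ways.

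- **Severity:** take each participant's worst grade, with 0 for no event, and compare arms by a Wilcoxon rank-sum test or a proportional-odds model, reporting the odds ratio with its 95% confidence interval.
- **Incidence:** for the percentage of participants with each event or abnormality, add the metformin-minus-placebo risk difference with a 95% Newcombe or exact interval. The chi-squared p-value may stay. State that safety will be interpreted from the interval.

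The cost is a change of wording and slightly different tables, using data already collected, with no extra participants or visits. The small downside is that the wide intervals make the uncertainty about safety more visible.

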## **10. Supporting Documentation and Operational Considerations**

### **10.1. Appendix 1: Regulatory, Ethical, and Study Oversight Considerations**

#### **10.1.1. Regulatory and Ethical Considerations**

- This study will be conducted in accordance with the protocol and with the following:
  - Consensus ethical principles derived from international guidelines including the Declaration of Helsinki and Council for International Organizations of Medical Sciences (CIOMS) International Ethical Guidelines
  - Applicable ICH Good Clinical Practice (GCP) Guidelines
  - Applicable laws and regulations
- The protocol, protocol amendments, ICF, Investigator Brochure and other relevant documents (e.g., advertisements) must be submitted to an IRB/IEC by the investigator and reviewed and approved by the IRB/IEC before the study is initiated.
- Any amendments to the protocol will require IRB/IEC approval before implementation of changes made to the study design, except for changes necessary to eliminate an immediate hazard to study participants.
- Protocols and any substantial amendments to the protocol will require health authority approval prior to initiation except for changes necessary to eliminate an immediate hazard to study participants.
- The investigator will be responsible for the following:
  - Providing written summaries of the status of the study to the IRB/IEC annually or more frequently in accordance with the requirements, policies, and procedures established by the IRB/IEC
  - Notifying the IRB/IEC of SAEs or other significant safety findings as required by IRB/IEC procedures
  - Providing oversight of the conduct of the study at the site and adherence to requirements of 21 CFR, ICH guidelines, the IRB/IEC, European regulation 536/2014 for clinical studies (if applicable), European Medical Device Regulation 2017/745 for clinical device research (if applicable), and all other applicable local regulations

#### **10.1.2. Financial Disclosure**

Investigators and sub-investigators will provide the sponsor with sufficient, accurate financial information as requested to allow the sponsor to submit complete and accurate financial certification or disclosure statements to the appropriate regulatory authorities.

### 10.1.3. Informed Consent Process

- The investigator or his/her representative will explain the nature of the study to the participant and answer all questions regarding the study.
- Participants must be informed that their participation is voluntary. Participants will be required to sign a statement of informed consent that meets the requirements of local regulations, ICH guidelines, Health Insurance Portability and Accountability Act (HIPAA) requirements, where applicable, and the IRB/IEC or study center.
- The medical record must include a statement that written informed consent was obtained before the participant was enrolled in the study and the date the written consent was obtained. The authorized person obtaining the informed consent must also sign the ICF.
- Participants must be re-consented to the most current version of the ICF(s) during their participation in the study.
- A copy of the ICF(s) must be provided to the participant
- A participant who is rescreened is not required to sign another ICF if the rescreening occurs within (30) days from the previous ICF signature date.

The ICF will contain a separate section that addresses the use of remaining mandatory samples for optional exploratory research. The investigator or authorized designee will explain to each participant the objectives of the exploratory research. Participants will be told that they are free to refuse to participate and may withdraw their consent at any time and for any reason during the storage period. A separate signature will be required to document a participant's agreement to allow any remaining specimens to be used for exploratory research. Participants who decline to participate in this optional research will not provide this separate signature.

